# Efficacy of the erector spinae plane (ESP) block for quality of recovery in posterior thoraco-lumbar spinal decompression surgery: study protocol for a randomised controlled trial

**DOI:** 10.1186/s13063-021-05101-2

**Published:** 2021-02-17

**Keywords:** Erector spinae plane block, Spine surgery, Quality of recovery, Morbidity, Analgesia

## Abstract

**Background:**

Spinal surgery can be associated with significant postoperative pain. Erector spinae plane (ESP) block is a new regional anaesthesia technique, which promises effective postoperative analgesia compared with systemically administered opioids, but has never been evaluated in terms of patient-centred outcomes such as quality of recovery and overall morbidity after major thoraco-lumbar spinal surgery.

**Methods:**

We are conducting a prospective, randomised, double-blind trial in two hospitals in the Republic of Ireland. The sample size will be 50 patients (25 in the intervention group and 25 in the control group). Randomisation will be done using computer-generated concealed envelopes. Both patients and investigators collecting outcome data will be masked to group allocation. Participants will be male or female, aged 18 years and over, capable of providing informed consent and ASA grade I–IV. Patients scheduled to undergo posterior approach thoraco-lumbar decompression surgery involving 2 or more levels will be recruited to the study. Participants randomised to the intervention arm of the study will receive bilateral ultrasound-guided ESP block totalling 40 ml 0.25% levo-bupivcaine (20 ml each side), post induction of general anaesthesia and before surgical incision. The control group will not receive an ESP block. Both groups will receive the same standardised analgesic protocol both intra- and postoperatively. The primary outcome will be the quality of recovery at 24 h postoperatively as determined by the QoR-15 score. This score is determined by a questionnaire which measures patient responses to 15 subjective parameters, each response graded on a scale from 0 to 10. The maximum score achievable is 150 with a potential minimum score of 0. Higher scores indicate a higher quality of recovery experience.

Secondary outcomes will include area under the curve (AUC) of VRS pain versus time at rest and on movement up to 24 h postoperatively, 24 h opioid consumption, time to first analgesia in recovery, length of stay (LOS), incidence and severity of postoperative complications as measured by the Comprehensive Complication Index (CCI) score.

**Discussion:**

To the best of our knowledge, this will be the first randomised control trial to examine the efficacy and safety of the ESP block in terms of patient-centred outcomes in the setting of major spinal surgery. The QoR-15 is a validated means of assessing the quality of recovery after surgery and gives a more holistic assessment of the recovery experience from the patient’s point of view.

**Trial registration:**

This trial is pre-registered on ClinicalTrials.gov reference number NCT04370951. Registered on 30 April 2020. All items from the World Health Organisation Trial Registration Data Set have been included.

**Supplementary Information:**

The online version contains supplementary material available at 10.1186/s13063-021-05101-2.

## Background

Major spine surgery is acknowledged to be associated with moderate to severe postoperative pain. A prospective cohort study of patients undergoing spinal surgery reported median verbal response scale (VRS) pain scores ranging from 5 to 7 on the first postoperative day [1]. Severe postoperative pain is associated with considerable morbidity, prolonged length of in-hospital stay (LOS), increased opiate requirements and prolonged time to mobilisation.

Recently, a novel regional anaesthesia technique has been described for patients undergoing spinal surgery. First described by Forero in 2016 for the treatment of thoracic neuropathic pain, the erector spinae plane (ESP) block involves depositing local anaesthesia under ultrasound guidance on the transverse process of the thoracic vertebrae, deep to the erector spinae muscle complex [2]. Cadaveric and MRI studies suggest that ESP can block the posterior rami of the spinal nerves in addition to the anterior spinal nerve rami to the paravertebral and epidural spaces, although this seems less consistent [3–5]. The posterior ramus of the spinal nerves provides sensory innervation of the paraspinal muscles, soft tissue and skin at the level at which it emerges [6]. This is of particular relevance in spinal surgery, because these structures must be incised and retracted in order to gain appropriate surgical exposure.

The evidence base for ESP in spine surgery is sparse. The published literature that currently exists reports lower VRS pain scores postoperatively among those patients receiving ESP compared with systemic opioids [7–10]. While lower pain scores are important, they may not be perceived by the patient as a better recovery if they are accompanied by other debilitating side effects such as subjective lack of wellness, depression, nausea, constipation or delirium. Pain scores alone are an insensitive marker of the quality of a patient’s recovery after major surgery.

Recent best practice in anaesthesia and perioperative medicine research has been to adopt a more holistic and patient-centred approach to the evaluation of the recovery experience. The QoR-15 score is internationally recognised as a validated means of assessing patients’ quality of recovery after surgery [11]. The score assesses 5 domains of patient-reported health status: pain, physical comfort, physical independence, psychological state and emotional state to give a holistic assessment of the patient’s overall recovery experience.

Currently, opiate therapy is the primary treatment option for patients suffering acute postoperative pain after major spinal surgery. Adverse events associated with high opioid requirements postoperatively are well documented and include nausea, constipation, respiratory depression, lower respiratory tract infections and drug dependency [12]. Available evidence to date suggests the ESP block may have opioid-sparing properties [7, 9, 10], making it an attractive option in spine surgery that merits further investigation.

Additionally, the ESP block appears to be relatively simple to perform and is associated with few adverse events [13]. Alternative regional techniques such as epidural and paravertebral anaesthesia are technically more challenging to perform and are associated with significant safety risks, such as epidural haematoma or pneumothorax [14–16]. While the ESP block has been adopted enthusiastically by many anaesthesiologists, evidence showing its efficacy in improving the recovery experience and reducing morbidity for patients is lacking and therefore this clinical trial is warranted.

We hypothesise that ESP block provides superior quality of recovery and reduced morbidity compared with systemic analgesia alone. This is based on the scientific rationale that it blocks both posterior and anterior rami of the spinal nerves, thereby providing extensive block and better analgesia.

We propose a prospective, two-centre, randomised control trial of 50 patients scheduled for posterior approach thoraco-lumbar spinal surgery. The co-primary outcomes will be QoR-15 score at 24 h postoperatively and postoperative complications as measured by the Comprehensive Complication Index (CCI) score.

Secondary outcomes include area under the curve (AUC) of VRS pain versus time at rest and on movement up to 24 h postoperatively, 24 h opioid consumption, time to first analgesia in recovery and length of stay (LOS). This paper describes the protocol for the intended trial.

## Methods and analysis

The trial protocol has been prepared and is reported in accordance with the SPIRIT PRO extension reporting guidelines [17]. The schedule of enrolments, interventions and assessments is outlined in Fig. 1. The SPIRIT checklist is included as an additional file.

**Fig. 1 Fig1:**
[figure not shown]
Overview of assessment. Recommendations for Interventional Trials (SPIRIT) Figure showing the schedule of enrolment, interventions and assessment

### Study objectives

#### Primary aims

We aim to complete a randomised control trial to test the hypothesis that the erector spinae plane block (combined with systemic analgesia) provides superior quality of recovery as measured by the QoR-15 score.

#### Secondary aims

Secondary aims are to discover whether the ESP block has favourable outcomes on other metrics of patient-centred patient outcome: area under the curve (AUC) of VRS pain versus time at rest and on movement up to 24 h postoperatively, 24 h opioid consumption, time to first analgesia in recovery, length of stay (LOS) and incidence and severity of postoperative complications as measured by the Comprehensive Complication Index (CCI) score.

### Study design

This is a prospective, double-blind (participant and investigator), randomised controlled clinical trial. Two centres will participate. Recruitment commenced on 1 May 2020, and total recruitment is expected to take 9 months.

### Study setting

The study setting comprises two tertiary level hospitals in the Republic of Ireland. Each hospital performs over 200 spinal surgeries per year.

### Randomisation and blinding

Patients will be randomised to one of the trial groups using computer-generated random number tables. Numbers ending in an even number integer will be designated to receive an ESP block; odd numbers will be allocated to the control group. The patient study number and group allocation will be typed on separate pages, folded and concealed in sequentially numbered sealed opaque envelopes. Block randomisation in groups of 6 will be applied to ensure an even number in each group as the study progresses. The groups will be named “ESP” erector spinae plane and “control”. A randomisation key will be held by an independent third party. Investigators will not have access to the randomisation key until all data is collected.

After induction of general anaesthesia, the envelope will be opened by the treating anaesthesiologist to reveal the group allocation. The investigators, patients and researchers involved in data collection will be masked to group allocation. The attending anaesthesiologist will not be blinded to the group allocation. Group allocation will be revealed immediately if deemed clinically necessary, for example, if a concern regarding local anaesthetic toxicity arises.

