### Selection of participants

#### Recruitment

Potential participants will be screened by the surgical and anaesthetic teams who will then inform a member of the research team of the potential availability of the patient for the trial. A member of the research team will then approach the patient, confirm the initial screening for suitability and then obtain informed consent for study participation if the patient wishes to be involved in the study. Participants will be informed that their participation in the study is entirely voluntary and they are free to withdraw from the study at any time and this will have no bearing on the quality of care they receive. Patients who are unable to give informed consent due to cognitive impairment will be excluded from the trial. Patients who do not speak English will be enrolled to the trial if an interpreter is present and the patient gives informed consent through the interpreter.

Active participation in the study will be until 30 days postoperatively. At 24 h, patients will be asked to complete the QoR-15 questionnaire.

Postoperative complications will be graded using the Comprehensive Complication Index calculator (CCI^R^). This data will be acquired by using our electronic patient record system to remotely track the progress of our patients in the postoperative period. Patient progression will be monitored for the entirety of their hospital stay or for 30 days post surgery (whichever is longer).

Once the patient is discharged from hospital, there will be no further data collection. Where there is a breach in trial protocol this data will not be analysed.

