### Study intervention

Participants randomised to the ESP group will receive an ultrasound guided bilateral ESP block post induction of general anaesthesia and prior to commencement of surgery. Blocks will be performed under full asepsis with patients in the prone position. Twenty millilitres of 0.25% levobupivacaine will be injected bilaterally at the level corresponding to the mid-point of the range of surgical dermatomes likely to be affected by the surgery. Typically, ESP will be administered at T6 level (total 40 ml). The ESP block will be performed as follows:

The approximate midpoint of the intended surgical incision will be identified first. The ultrasound transducer will then be placed approximately to 2–3 cm lateral to the midline in a longitudinal orientation to identify the hyperechoic line of the transverse process with its associated acoustic shadow. After identification of trapezius, rhomboid major and erector spinae muscle groups superficial to the transverse process, an echogenic needle will be advanced in a cranio-caudal direction. The needle tip will be advanced until it is located in the interfascial plane deep to the erector spinae muscle group and superficial to the transverse process. Once in position, 20 ml 0.25% levobupivicaine will be injected under ultrasound guidance. Correct needle tip position will be confirmed by the presence of linear spread between the transverse process and the erector spinae muscle group. The same process will then be repeated on the opposite side at the same vertebral level. Because patients will be under general anaesthesia during the block performance, no formal dermatomal sensory testing of block efficacy will be performed. Surgery will commence once the block is completed. There will be no further intervention to the routine conduct of surgery and anaesthesia after this point. Blocks will be performed by anaesthesiologists with subspeciality training in regional anaesthesia. To improve adherence to the intervention protocol, anaesthesiologists will be asked to document the block performance in the anaesthesiology patient record. Although the ESP has been established as a safe means of providing analgesia in spine surgery, we will make all our data available to local data monitoring committee.

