### Outcome measures

Quality of recovery will be measured using the QoR-15 questionnaire. Postoperative pain will be quantified using a verbal response scale (VRS) ranging from 0 to 10, where 0 equals “no pain at all” and 10 equals “the worst pain imaginable”. Reported pain scores will then be plotted against time to give the AUC of pain versus time. Pain scores will be recorded at 6, 12 and 24 h post surgery at rest and on movement.

Postoperative complications will be graded using the Comprehensive Complication Index calculator (CCI^R^). This data will be acquired using our electronic patient record system to remotely track the progress of our patients in the postoperative period. Patient progression will be monitored for the entirety of their hospital stay or for 30 days post surgery (whichever is longer).

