### Sample size and justification

The primary outcome of this study will be the QoR-15 score at 24 h postoperatively. The established minimum clinically important difference in QoR-15 is 8.0 and the mean SD of QoR-15 scores after major spinal surgery is in the order of 14 [range of QoR score is 1–150]. Therefore, assuming type I error = 0.05 and type II error = 0.2 (80% power to detect this difference), then *n* = 25 patients will be required in each group. To accommodate for participants who may withdraw from the study, we will aim to recruit *n* = 26 patients to each study arm.

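### The allocation method is stated ambiguously, fixed blocks of 6 let some allocations be inferred, and outcome staff are not shielded from the record of the nerve block

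*Protocol article*

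**What the plan says.** **Generation.** Under Randomisation and blinding, the protocol article takes random numbers from computer-generated tables and gives this rule: "Numbers ending in an even number integer will be designated to receive an ESP block; odd numbers will be allocated to the control group". Three sentences of the same paragraph later it adds: "Block randomisation in groups of 6 will be applied to ensure an even number in each group as the study progresses". No other block size is mentioned. The article does not say whether there is one list or one per hospital.

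**Concealment.** Study number and arm are "folded and concealed in sequentially numbered sealed opaque envelopes". An independent third party holds the key. The treating anaesthesiologist opens the envelope after induction and is unmasked from then on. Patients, investigators and data collectors are to be masked.

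**Referral.** Under Recruitment: "Potential participants will be screened by the surgical and anaesthetic teams". A member of the research team then confirms suitability and takes consent.

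**Records.** Under Study intervention: "anaesthesiologists will be asked to document the block performance in the anaesthesiology patient record". The data list under Patient and process characteristics includes timings, blood pressure and heart rate extremes, total intraoperative opioid, and complications attributable to the ESP block. For the Comprehensive Complication Index (CCI), Outcome measures says: "This data will be acquired using our electronic patient record system to remotely track the progress of our patients in the postoperative period".

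**The concern.** There are three separate issues, each with its own cause.

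1. **Two generation rules.** Assigning arms by the parity of independent random numbers is simple randomisation, which does not balance each six patients. Blocking does. A reader cannot tell which sequence was produced, or whether the study number that accompanies each patient is the number whose parity sets the arm.

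2. **Inference of upcoming allocations.** With one known block size, anyone who has seen the earlier allocations in a block can sometimes deduce the next. The people who see allocations are anaesthesiologists, and the anaesthetic teams help decide who is put forward. The stake is selection bias at referral, before consent.

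3. **Masking of outcome staff.** The described data flow could take masked staff to records that show whether a nerve block was given. The stake is detection bias in outcomes that depend on an assessor. CCI matters here because it grades severity, and because the Background calls it co-primary with QoR-15, while the abstract and Secondary aims list it as secondary.

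**Working it through.** The article gives no figure for balance or predictability, so there is none to reproduce. Inputs from the article: 1:1 allocation, blocks of 6, a total of 50 (abstract), or 52 at 26 per arm (Sample size and justification). Assumption: each block is 3:3, as the aim of equal groups implies.

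**1. What parity alone would give**
- 3:3 in a given six: C(6,3)/2^6 = 20/64 = 31.3%.
- 25:25 in fifty: C(50,25)/2^50 = 11.2%.
- 28:22 or more unequal in fifty: binomial(50, 0.5) tails = 48.0%.

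Blocks of 6 make every complete six 3:3. Only the last, incomplete block can be uneven (one list assumed):
- 50 = 8 × 6 + 2, so P(25:25) = 2 × 3 × 3/(6 × 5) = 60%; otherwise 26:24.
- 52 = 8 × 6 + 4, so P(26:26) = C(3,2)²/C(6,4) = 9/15 = 60%; otherwise 27:25.

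The two rules therefore give materially different sequences unless combined. They can be combined: parity could fill a block until one arm has three, with the rest going to the other arm. The article does not say this.

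**2. What a fixed block of 6 reveals**

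Take all C(6,3) = 20 orderings as equally likely, and an observer who knows the block size and every earlier allocation in the block. An allocation is certain once one arm has reached three:
- 4th place: 2/20 = 0.1
- 5th place: 8/20 = 0.4
- 6th place: 20/20 = 1

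Total 1.5 of 6 = **25% certain**.

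If parity draws filled the block until an arm closed, the orderings would not be equally likely: 4th place 2 × (1/2)³ = 0.25, 5th place 0.25 + 0.75 × 0.5 = 0.625, 6th place 1, so 1.875/6 = 31%. The answer to point 1 therefore also affects this figure.

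Best-guess rate, always naming the arm that is behind, with equally likely orderings: 0.5 + 0.6 + 0.6 + 0.7 + 0.7 + 1.0 = 4.1 of 6 = 68.3%, against 50% by chance.

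For varied sizes 4, 6 and 8 (assumed for illustration), expected correct guesses per block are 2.83, 4.10 and 5.33, so 12.26/18 = 68.1%. A simulation of 52 allocations with these sizes, in which the guesser used only the running imbalance, gave 67.8%. Varying the size hardly changes the guess rate. It mainly removes certainty.

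**3. Masking set beside data flow**
- Stated: data collectors do not know the arm.
- Stated: the nerve block is written in the anaesthesiology record.
- Stated: intraoperative opioid, timings and haemodynamics are collected. Their source is not named; the anaesthesiology record is the likely one.
- Stated: CCI comes from the electronic patient record, and ESP-related complications are recorded.
- Not stated: any step that keeps the nerve-block entry from the staff who collect or grade.

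QoR-15 is completed by patients who were under general anaesthesia when the block was given, so the record route bears little on it.

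**The case against.** **A reader might infer that the two rules contradict each other and so make allocation predictable.** The text does not support that. Parity can order patients within a block, so this is an ambiguity. Parity of random numbers is also unpredictable in itself. It would reveal the arm only if the parity number were the visible study number, which the article does not say. Because the article says blocking is applied, the 11% and 48% describe a reading it probably does not intend. They show only that the two sentences need reconciling.

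**Concealment is described with real safeguards.** Sealed opaque numbered envelopes, a third-party key and opening after induction protect the current envelope, and a research-team member takes consent. This stands. The safeguards do not stop deduction from earlier envelopes. That deduction needs the full block history, however, and no passage says one person holds it. If one list spans both hospitals, staff at either see only part of it. The article also does not say that site staff were told the block size.

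**The 68% rate is no argument for varied blocks**, because it is about 68% either way. This stands.

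**Unmasking through the record is not proven.** The article does not say that the anaesthesiology record and the electronic patient record are one system, or who extracts the intraoperative data. Exposure is likely, not established. A reader might go further and conclude that the primary outcome is unblinded. The documents do not support that: QoR-15 is self-reported, and the Discussion says its assessors are blinded.

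**Timing.** Recruitment was expected to end by 31 January 2021 and the article is dated 17 February 2021, so few or no envelopes may remain.

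**Conclusion.** The concern holds as three modest, separate points.

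1. The generation method is not determinable from the text. If parity draws were independent, the promised balance would not follow (3:3 in a given six with probability 31%, 25:25 in fifty with 11%).
2. Fixed blocks of 6 with unmasked openers from teams that also screen allow partial inference. For an observer with the full block history, 25% of allocations are certain, assuming 3:3 blocks with equally likely orderings. With incomplete history the share is lower.
3. The masking statement and the described data flow do not fit together for record-based outcomes. The exposure is mainly CCI and staff-collected pain scores. It assumes that collectors or graders can reach the nerve-block entry, which the article neither states nor rules out.

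None of this shows that allocation was in fact predicted or that an assessor was unmasked. It is worth acting on because the changes are cheap and make the double-blind description easier to defend.

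**What to change.** 1. **Generation.** State the one method actually used, including how parity and blocks combine if both were used. Confirm that study numbers do not encode the arm. Cost: a few sentences.
2. **Sequence.** For any unopened envelopes, have the independent third party prepare one list per hospital with randomly varying block sizes not disclosed to site staff, and adjust the primary analysis for hospital. Patients already randomised keep their allocations. This mainly removes certainty and does not lower the best-guess rate. Cost: re-printing the unopened envelopes and one covariate. If none remain, report the method and block size as used.
3. **Masking.** Leave the clinical note of the nerve block where it is. Have the treating anaesthesiologist, who is already unmasked, transcribe intraoperative data to a form without the nerve-block entry. Grade CCI from an extract that excludes the anaesthetic record. Cost: one extra form and preparation of the extract.
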